#### **9.2.1 Primary outcome analysis**

- The primary objective of this study is to assess the safety of administering sulfasalazine in patients with preterm preeclampsia
- We will assess for adverse effects in the mother and the fetus/neonate
- We will assess mortality and morbidity outcomes - including neurological, respiratory, eye disorders and gastrointestinal disease - in the fetus/neonate
- We will also assess the pharmacokinetic profile of sulfasalazine which will involve taking maternal serum levels of sulfasalazine following administration; maternal urinary excretion of sulfasalazine following administration; and maternal serum levels, cord blood levels and placental levels of sulfasalazine at delivery
- Pharmacokinetic parameters include maximum concentration (C-max); time to maximum concentration (T-max); area under the concentration time curve (AUC); apparent oral clearance (CL/F); half-life; and renal clearance.

#### **9.2.2 Secondary outcome analyses**

- The secondary objective will be to determine the effects of sulfasalazine on clinical and biochemical markers of preeclampsia disease progression.
- In the mother, we will assess length of gestation prolongation compared to a contemporaneous cohort; occurrence of clinical symptoms; and the progression of biochemical aspects of disease (including liver function, renal function, proteinuria and haematological parameters).
- For participants recruited at MHW, we will measure brachial artery flow-mediated dilatation as a surrogate measure of maternal endothelial function
- Furthermore, we will assess biomarkers of preeclampsia (including sFlt-1 and sENG) in maternal blood samples from recruitment until delivery

### 9.2.3 Missing data/sensitivity analyses

Missing data will be presented descriptively.

### 9.2.4 Subgroup analyses

This study will not be powered to perform subgroup analyses.

### 9.2.5 Interim analysis

An interim analysis will not be conducted for this study.

### 9.2.6 Final analysis

A final analysis will be conducted by the trial Investigators.

## 10 ADVERSE EVENTS

The Manufacturer's Product Information (see *Appendix 1*) for Salazopyrin EN contains the full details of the known contraindications and side effects that have been reported following the administration.

Participants who are recruited to the trial will be instructed to inform their direct clinical care team or a member of the research team at any time during their participation if they develop symptoms, whether or not they think these may be related to sulfasalazine. All AEs that occur after consenting to the trial must be logged in detail in the CRF or recorded in an AE log. In the case of an AE which may be related to the administration of the IMP, a medically-qualified Investigator will initiate any appropriate treatment(s), according to their clinical judgement.

The Site Leaders are responsible for the detection, documentation and follow-up of events experienced by volunteers (at their respective hospitals) during their participation in the study that meet the criteria and definitions as detailed below.

### 10.1 DEFINITIONS

This trial is being undertaken with the approval of the Mercy Health HREC and the TGA's CTN scheme. Adverse events will be managed according to the following definitions, recommendations and requirements, guided by ICH-GCP principles, TGA guidelines (19), and the National Health and Medical Research Council (NHMRC)'s *National Statement* (20).

An **Adverse Event** (AE) is any untoward medical occurrence in a study participant who has been administered an IMP. An AE does not necessarily have a causal relationship with the IMP in question.

An **Adverse Drug Reaction** (ADR) is any unintended, noxious response to an IMP at any dose, where a causal relationship between the IMP and the reaction cannot be ruled out.

A **Serious Adverse Event** (SAE) or **Serious Adverse Drug Reaction** (SADR) is defined as any AE or ADR that:

- Results in the death of a participant;
- Is life-threatening (puts the participant at risk of death of the time of the event – it does not refer to an event which could have hypothetically ended in death, had the event been more severe);
- Requires inpatient hospitalisation, or prolongation/escalation of existing hospitalisation;
- Results in a congenital abnormality or birth defect; or
- Results in significant or persistent incapacity/disability

An **Unexpected Adverse Drug Reaction** (UADR) is an ADR, the nature or severity of which is not consistent with the available manufacturer's Product Information (*Appendix 1*).

A **Suspected, Unexpected, Serious Adverse Reaction** (SUSAR) is any ADR that is:

- Classified as serious;
- Suspected to be caused by the IMP; and
- Not consistent with the information available in the manufacturer's Product Information

## 10.2 IDENTIFYING AEs AND SAEs

All AEs/SAEs will be recorded from the time a participant signs the consent form until their postnatal closing out visit or phone call has been completed. Worsening of preeclampsia disease indicators that follow the normal, expected clinical course of the disease will not be reported as an AE/SAE, but will be recorded in the CRF. Any AE must be recorded on the AE log page in the CRF. Antenatal admission to hospital will not be considered as an AE/SAE, as it follows the course of normal clinical management for this cohort. An escalation of hospitalisation (e.g. from general ward to intensive care) as a result of an ADR will be classified as a SAE/SADR.

Participants will be asked about the occurrence of AEs/SAEs at every research team contact episode during the study, using open-ended and non-leading questions (e.g. "Tell me about how you've been feeling"), as well as specific questions relating to any occurrence of common ADRs (e.g. gastrointestinal symptoms). Participants' medication charts will be reviewed to assess for study protocol compliance, as well as any major changes to concomitant medications. AEs/SAEs may also be identified via information from the medical history or other source documents (e.g. abnormal pathology test results not consistent with the woman's preeclampsia disease progression, such as aplastic anaemia). If there is any doubt whether or not an event or clinical observation constitutes an AE, the event will be recorded as an AE.

Known, common gastrointestinal side effects of sulfasalazine therapy (nausea, vomiting, diarrhoea) will be noted on the CRF but do not need to be recorded as AEs, unless meeting the criteria for a 'serious' or 'severe' event (see *Section 10.1*).

Some known, advanced side effects of sulfasalazine therapy (e.g. convulsions) may mimic signs and symptoms of worsening preeclampsia/eclampsia. It is not anticipated (based on the Manufacturer's Information – *Appendix 1*) that participants in this study will be receiving a high enough dose of sulfasalazine for long enough to develop these advanced side effects. Any occurrence of a convulsion in a study participant should be medically managed as a presumed eclamptic fit. However, because the relationship between any such event in a study participant taking sulfasalazine cannot be absolutely excluded as a SADR/SUSAR, it must still be recorded in the CRF, the AE log in the ISF and reported to the PIs, HREC and the TGA (as appropriate) as a SADR/SUSAR event (see *Sections 10.3-10.5*). The subsequent assessment of causality (see *Section 10.4.2*) may then deem the event to be an 'unlikely' SADR/SUSAR, and more probably the result of the progression of severe preeclampsia disease.

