### **2.1 OBJECTIVES**

#### **2.1.1 Primary objectives**

The primary objective of this study is to establish the safety and pharmacokinetic profile of sulfasalazine in patients with preterm preeclampsia. In particular, we will be examining:

- Any adverse effects in the treated mother (safety data)
- Fetal/neonatal mortality and morbidity outcomes of participants' babies; including neurological, respiratory, eye and gastrointestinal disease (safety data)
- Maternal plasma and urine levels of circulating and excreted sulfasalazine following dose administration (pharmacokinetic data)
- Maternal blood, cord blood and placental levels of sulfasalazine following delivery (pharmacokinetic data)

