Participants will be visited every 1-3 days from recruitment until delivery (while they remain inpatients) by a member of the research team to monitor for AEs or possible side effects of sulfasalazine, and to ensure the participant's ongoing willingness to participate in the trial. Participants who are discharged home prior to the birth of their baby will be reviewed by a researcher each time they attend their hospital for an outpatient review until they are readmitted or their baby is born. A member of the research team will be on call to attend or for advice relating to concerns raised by the participants or the clinicians providing their direct care.

Biochemical markers of preeclampsia disease (such as LFTs and proteinuria) will be monitored as a part of standard clinical care. The researchers will also have access to these routine pathology results – this data forms some of the secondary outcomes of the study.

The timing of delivery and any deviations from routine clinical care will be determined by the treating clinician or obstetric unit – not by a member of the research team. In the case where a member of the research team is also acting as the treating clinician, these decisions will be made in consultation with other members of the treating obstetric unit, with the best interests of mother and baby as the paramount consideration.

The medical histories of babies born to participants (including any pathology results from tests ordered by the treating clinicians) will be reviewed postnatally to assess for neonatal outcomes and AEs. A 'closing out' visit on the postnatal ward (or phone call following maternal discharge) will be made following the delivery of each participant's baby.

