## 7.2 SUMMARY TABLE OF STUDY ASSESSMENTS

TABLE 2: Summary of study assessments

|                                         | Prior to treatment commencement | 1 st day of treatment | After 30 hours of treatment | Each subsequent review | Day of delivery (or next weekday) | Closing out visit/phone call |
|-----------------------------------------|---------------------------------|----------------------------------|-----------------------------|------------------------|-----------------------------------|------------------------------|
| Consent                                 | ✓                               | ✓*                               | ✓*                          | ✓*                     | ✓*                                | ✓*                           |
| Medical history review                  | ✓                               | ✓                                | ✓                           | ✓                      | ✓                                 | ✓                            |
| Check results: Clinical pathology tests | ✓                               | ✓                                | ✓                           | ✓                      | ✓                                 | ✓                            |
| Flow-mediated dilatation (MHW)          | ✓                               |                                  | ✓                           |                        |                                   |                              |
| Sulfasalazine levels                    |                                 |                                  | ✓**                         |                        | ✓***                              |                              |
| Biomarkers of PE                        | ✓                               | ✓                                | ✓                           | ✓                      | ✓                                 |                              |
| Adverse events                          |                                 | ✓                                | ✓                           | ✓                      | ✓                                 | ✓                            |

|                                |  |   |   |   |   |   |
|--------------------------------|--|---|---|---|---|---|
|                                |  |   |   |   |   |   |
| IMP regime compliance   |  | ✓ | ✓ | ✓ | ✓ |   |
| Neonatal history review |  |   |   |   | ✓ | ✓ |

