### 7.3 LONG TERM FOLLOW UP ASSESSMENTS

At the time of application, there are no plans for long term follow up of the study cohort.

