## **14.5 END OF STUDY**

The 'end of study' for this trial is defined as the last point of direct patient contact between the research team and the participants for data collection purposes. This would likely be the date of the postnatal closing out visit or phone call made to the final remaining participant in the study.

However, the TSC, DSMC and/or the Sponsor have the right to terminate the trial at any time prior to this point for clinical safety or administrative reasons. The date of trial termination would then constitute the 'end of study' date.

The end of study date will be reported to HREC within 90 days of completion; or within 15 days if the trial is terminated prematurely. The Site Leaders will inform participants in the instance of a premature study closure and ensure that any appropriate follow up is arranged for all participants involved.

A summary report of the study will be disseminated within 1 year of the completion of the trial, as described in *Section 15.2*.

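### The window for the primary neonatal safety outcome is undated and ends at the mother's close-out, and the adverse event definitions do not settle whether fetal or neonatal death is a serious event

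*Protocol*

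**What the plan says.** Section 2.1.1 of the Protocol places this under the primary objective: "Fetal/neonatal mortality and morbidity outcomes of participants' babies; including neurological, respiratory, eye and gastrointestinal disease (safety data". Section 9.2.1 repeats it for the primary analysis.

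The time limits on observation are set elsewhere, and they refer to the mother:

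- Section 10.2 records adverse events from consent "until their postnatal closing out visit or phone call has been completed".
- Section 3 describes the close-out as a "visit on the postnatal ward (or phone call following maternal discharge) will be made following the delivery". It gives no day.
- Table 2 (Section 7.2) has a row "Neonatal history review", ticked on the day of delivery and at close-out. There is no later column.
- Section 14.5 defines end of study as "the last point of direct patient contact between the research team and the participants for data collection purposes", and expects this to be the final close-out contact.
- Section 7.3 says "there are no plans for long term follow up of the study cohort".

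On what counts as an event, Section 10.1 defines an adverse event as "any untoward medical occurrence in a study participant who has been administered an IMP". The death and life-threatening criteria for seriousness also refer to the participant. Congenital abnormality or birth defect is a separate criterion. The clinical endpoints in Section 2.2.2, by contrast, list adverse events in the baby as well as the mother.

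**The concern.** A safety rate needs a defined period at risk. Here it is whatever time passes between birth and an undated contact with the mother. Babies whose mothers are closed out at different times are observed for different lengths of time, and a pooled neonatal rate out of 20 has no stated meaning in time. Section 1.4.1 names chronic lung disease, retinopathy of prematurity and necrotising enterocolitis among the complications of prematurity. Any such event that first appears after close-out is not scheduled to be found. The error runs in one direction only: the count can be too low, never too high.

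The second issue is classification. If the woman is the only participant, the wording of 10.1 leaves open whether a stillbirth or neonatal death is a serious adverse event. That decides whether the 24-hour notice to the principal investigators (10.4, 10.5) and the 7- and 15-day reports to the ethics committee and regulator (10.6) apply.

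**Working it through.** **1. The window.** No rule in 3, 7.2, 10.2 or 14.5 refers to the baby's age, discharge or death. Section 4.2 admits women at 30+0 to 36+0 weeks when treatment starts, so gestation at birth can vary by several weeks while the stopping rule does not take it into account.

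To show how the gap depends on gestation, I take 37+0 weeks as an arbitrary yardstick (not a discharge date) and assume close-out on day c = 1 to 14 after birth, since the Protocol states no day.

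Days unobserved before 37+0 = 37 × 7 − gestation at birth in days − c, floored at 0.

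| Birth at | Days to 37+0 | Unobserved, c = 1 | Unobserved, c = 14 |
|---|---|---|---|
| 30+0 (limiting case) | 259 − 210 = 49 | 48 | 35 |
| 33+0 | 259 − 231 = 28 | 27 | 14 |
| 36+0 | 259 − 252 = 7 | 6 | 0 |

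On this yardstick, the gap is longest for the earliest births and small or absent for the latest.

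**2. Effect on what is seen.** The Protocol's 20 rests on precedent and feasibility (9.1), with no power calculation (9.2), so there is no planned figure to reproduce. Let p be the true neonatal event rate and f the share of events arising after close-out, both assumed. Then P(at least one seen) = 1 − (1 − p(1 − f))^20.

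| p | f = 0 | f = 25% | f = 50% | f = 75% |
|---|---|---|---|---|
| 5% | 0.64 | 0.53 | 0.40 | 0.22 |
| 10% | 0.88 | 0.79 | 0.64 | 0.40 |

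For example, p = 10% and f = 50% gives 1 − 0.95^20 = 0.64. If 0 of 20 were observed, the exact two-sided 95% upper limit would be 1 − 0.025^(1/20) = 16.8%. That limit would bound harm up to close-out only. Each unseen affected baby is 1/20 = 5 percentage points.

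**3. The definitions side by side.**

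| Place | Whose events |
|---|---|
| 2.2.2 | Mother and baby |
| 9.2.1 | Mother and fetus or neonate |
| 10, opening text | Volunteers (Site Leaders' duty) |
| 10.1, adverse event | Participant given the drug |
| 10.1, death and life-threatening | Participant |
| 10.1, birth defect | Reaches the offspring |
| 10.1, adverse drug reaction | Not limited to a participant |
| 10.5, reporting trigger | Study participant |
| 12.4, periodic risk assessment | Mothers and babies |

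Sections 2.1.1 and 3 speak of babies as belonging to or born to participants, which suggests that the babies are not themselves participants. Section 12.4 describes the babies as enrolled too. The text does not settle the matter. The birth defect criterion does little to close the gap, because treatment starts at 30 weeks or later and known major malformations are excluded (4.3).

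**The case against.** Several provisions soften the problem, and they stand:

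- Section 3 says babies' histories are reviewed after birth for outcomes and adverse events, and Section 7 lists neonatal history review as an item separate from the close-out contact. Neither gives an end date, so a team could review later than Table 2 requires. Harm before close-out is collected as data.
- Section 10.7 follows any event already recorded to its outcome, with no limit at close-out. Only new events are exposed.
- Section 10.2 records doubtful events as adverse events, and the drug reaction wording in 10.1 is not confined to participants. A stillbirth could also be regarded as an untoward event in the treated woman.
- Section 12.4 has the steering and safety committees review babies' outcomes every 6 months.

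Three stronger readings are tempting, and the document does not support them. First, a reader might infer that the serious event definition ignores the offspring and that fetal or neonatal deaths are missed. The birth defect criterion and the record review contradict this; before close-out the doubt concerns classification and expedited reporting, not collection.

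Second, a reader might infer that observation covers only a small fraction of the neonatal stay. Close-out at day 3 to 7 and a stay of 4 to 8 weeks would give 3/56 = 5% to 7/28 = 25%, but neither range is in the Protocol, and share of stay is not share of events. The window is undated; it is not shown to be short.

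Third, a reader might infer that the safety committee is deprived of prompt notice. The 24-hour notice goes to the principal investigators for every serious event, maternal ones included.

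What the other side does not answer is that nothing is scheduled for the baby after close-out, and that a 6-monthly review is not expedited reporting and cannot show events that were never collected.

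**Conclusion.** The concern holds in two limited parts. The observation window for a primary neonatal safety outcome is undated and tied to the mother, so follow-up is unequal between babies and new harm after close-out has no planned capture. The resulting count can only be too low. By how much cannot be derived from the Protocol; the probabilities above rest on assumed event rates and assumed late shares, and the day counts on an assumed close-out day and an arbitrary yardstick.

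The Protocol also contradicts itself on whether the baby's events are adverse events. Apart from birth defects, it leaves open whether stillbirth or neonatal death triggers expedited reporting. No figure in the Protocol changes, but both parts concern primary safety data and should be settled by amendment.

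**What to change.** 1. Set one neonatal ascertainment point for every baby, for example first discharge home or death, met by record review. The choice of point is the team's; what matters is that it is defined by the baby and is the same rule for all.
2. Align the last neonatal history review in Table 2 and the neonatal adverse event window in 10.2 with that point. Adjust 14.5 if needed; it turns on direct contact, which a record review does not require.
3. In 10.1, extend the adverse event and serious adverse event definitions to the fetus and neonate, naming stillbirth, neonatal death and life-threatening neonatal events. State whether admission for prematurity alone is exempt, as 10.2 already does for antenatal admission.
4. Reconcile 2.2.2, the opening of Section 10, 10.1 and 10.2 so that all cover the same individuals, and match the reporting trigger in 10.5.

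The cost is a later record review of about 20 babies and a slightly later database lock. Consent wording, and access to records if a baby moves between hospitals, should be checked.

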### **6.3 DOSAGE CHANGES**

In the event that a participant experiences mild to moderate gastrointestinal side effects from taking sulfasalazine, but still wishes to participate in the trial, the dosage regime would be titrated down to a total of 2 grams per day in an attempt to mitigate the severity of the symptoms. If these symptoms resolve, the Site Leader may titrate the participant's dose back up to 3 grams daily according to their clinical judgement. Any participants who experience severe side effects associated with sulfasalazine therapy will be withdrawn from the study and revert to standard clinical management of preeclampsia. See *Section 10.4.4* for definitions of event severity.

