## **9 STATISTICS AND DATA ANALYSIS**

### **9.1 SAMPLE SIZE CALCULATION/RATIONALE**

The researchers plan to recruit 20 women with preterm preeclampsia over a period of 2 years. The researchers believe that this sample size is justified as follows:

- Many 'first in man' studies will recruit 10 to 20 participants. Whilst sulfasalazine is already given to pregnant women for other treatment indications, it has not yet been administered to an exclusively preeclamptic cohort
- 20 is a modest number, however it will be sufficient to obtain pharmacokinetic information and give preliminary data about sulfasalazine's capacity to have a clinical or biochemical effect on the disease mechanisms of preeclampsia
- A recent case report published in the American Journal of Obstetrics and Gynaecology (18) examined the effect of pravastatin in a sample size of 20 pregnant patients. This study primarily assessed the pharmacokinetics of pravastatin in pregnancy and also observed the incidence of preeclampsia
- The researchers are targeting preterm preeclampsia, which is a rarer occurrence than term preeclampsia. 20 participants is a realistic number that can be recruited over 2 years, when accounting for those cases that will inevitably decline inclusion or will be otherwise excluded from participating.

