### **9.2 PROPOSED ANALYSES**

Statistical analysis for this study will be performed using *GraphPad Prism 6* (GraphPad Software, La Jolla, CA). Given the study design and objectives of this particular trial:

- There is no comparison arm, so clinical variables and the clinical course will be presented as descriptive statistics
- There is no power calculation to perform
- Maternal and neonatal continuous variables will be statistically analysed using a t-test (parametric) or a Mann-Whitney test (non-parametric), as appropriate
- Categorical variables will be statistically analysed using a chi-squared test or Fisher's exact test, as appropriate
- Biomarker concentrations will be assessed as continuous variables
- Steady state sulfasalazine pharmacokinetic parameters will be estimated using standard non-compartmental techniques and normalized using actual body weights
- A p value of <0.05 will be considered statistically significant.

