### ***Investigations***

Induction of autoantibodies, elevation of liver enzymes.

\* Adverse effects are possibly dose-related.

\* Adverse effects identified post-marketing.

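### Section 10.2 exempts non-severe nausea, vomiting and diarrhoea from AE recording, against the protocol's own AE rules and its primary safety objective

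*Protocol*

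**What the plan says.** Section 2.1.1 lists under the primary objective "Any adverse effects in the treated mother (safety data", and section 9.2.1 carries adverse effects in mother and baby into the primary outcome analysis. Neither section says which record the analysis will be drawn from.

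Section 10 sets the general rule: "All AEs that occur after consenting to the trial must be logged in detail in the CRF or recorded in an AE log". Section 10.1 defines an AE as any untoward medical occurrence after the study drug, whether or not the drug caused it. Section 10.2 adds that any AE goes on the AE log page of the CRF.

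The same section 10.2 then makes two exceptions:

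- For common gastrointestinal effects: "nausea, vomiting, diarrhoea) will be noted on the CRF but do not need to be recorded as AEs". The exception lapses if the event is serious or severe, with a reference to section 10.1.
- For the disease: "Worsening of preeclampsia disease indicators that follow the normal, expected clinical course of the disease will not be reported as an AE/SAE". Such worsening is still recorded in the CRF.

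Section 6.3 begins its dosage-change rule with "In the event that a participant experiences mild to moderate gastrointestinal side effects from taking sulfasalazine" and refers to section 10.4.4 for severity.

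**The concern.** Nausea and vomiting head the list of most common side effects in Appendix 1. In a safety trial they are the events most likely to be seen, and they are the ones exempted by name. If the safety summary is built in the usual way from the AE log, sulfasalazine will look better tolerated than it was, on the primary outcome.

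The second exception raises a different worry. Appendix 1 lists as drug effects haemolytic anaemia, thrombocytopenia, hepatitis, proteinuria and, under Investigations, "Induction of autoantibodies, elevation of liver enzymes". Several of these are also features of preeclampsia or HELLP syndrome. If a change is judged to be expected disease, it is not reported as an AE. That judgement is made with knowledge of treatment (10.4), without a control arm, and with no threshold for what counts as expected.

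**Working it through.** There is no design figure to reproduce: "The researchers plan to recruit 20 women with preterm preeclampsia over a period of 2 years", and "There is no power calculation to perform". The check is mainly a comparison of sections.

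**1. Is a mild nausea episode on treatment an AE?** By 10.1, yes: it is an untoward occurrence, and the definition has no severity floor. By the log-page sentence in 10.2, it must then be logged. By the exemption in the same section, it need not be. The note in 10.4.4 uses nausea as its example of an AE that can be severe without being serious, so that section also treats nausea as an AE. The rule in 10.2 that doubtful events are recorded as AEs does not help, because these events are exempt by name and leave no doubt to resolve.

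**2. What does a CRF note lack that an AE record has?**

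| Item | Required for | Section |
|---|---|---|
| Onset date, temporality, dosage, treatment given, time to resolution, outcome | AEs and SAEs | 10.3 |
| Causality | AEs and SAEs | 10.4.2 |
| Severity grade | AEs and SAEs | 10.4.4 |
| Follow-up to a final outcome | recorded AEs, and SAEs | 10.7 |

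An event that is only noted on the CRF carries none of these as a stated requirement. Items not captured at the time may not be recoverable when the analysis is written.

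**3. Does the exemption work as written?** Staff must judge severity to know whether an event is exempt, yet 10.4.4 requires a grade only for AEs and SAEs. For the meaning of *severe*, 10.2 points to 10.1, which defines only *serious*; severity is defined in 10.4.4, where 6.3 correctly points. An effect that changes a woman's study dosing under 6.3 therefore need never be an AE.

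**4. Illustration of size.** The documents give no rate for these effects, so the rates below are assumptions. With n = 20 and true rate p, the expected number affected is 20p, and the chance of at least one is 1 − (1 − p)^20. Intervals are exact (Clopper-Pearson) 95% limits for the expected count.

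| Assumed p | Expected affected | P(at least one) | 95% CI for that count |
|---|---|---|---|
| 10% | 2/20 | 0.878 | 1.2% to 31.7% |
| 20% | 4/20 | 0.988 | 5.7% to 43.7% |
| 30% | 6/20 | 0.999 | 11.9% to 54.3% |
| 40% | 8/20 | >0.999 | 19.1% to 63.9% |

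If none of these events is severe or serious, an AE log kept to the letter of 10.2 could show 0/20, with a 95% upper limit of 1 − 0.025^(1/20) = 16.8%. This contrast arises only if the CRF notes are left out of the summary. Even then the intervals overlap: 0% to 16.8% against 11.9% to 54.3% in the 30% row. It shows the direction of the error and does not estimate its size.

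**5. Disease worsening.** Only worsening that follows the expected course is exempt. Doubtful events must be logged as AEs. Laboratory results inconsistent with disease progression are named as a source of AEs. Every convulsion must be recorded and reported first and attributed afterwards. What remains is the overlap: a rise in liver enzymes or a fall in platelets that fits preeclampsia but is due to the drug.

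**The case against.** The best case for the plan is that nothing is lost. Both exempt categories go into the CRF. Participants are asked specifically about gastrointestinal symptoms at every research contact, and severe or serious events remain AEs. The primary outcome is worded as adverse effects, not as entries on the AE log, and acceptability and side effects are an endpoint in their own right (2.2.2). Which CRF fields feed the safety table is normally settled in a statistical analysis plan, which is not at hand. The general rule in section 10 accepts the CRF as a place of record, so a CRF note meets most of it; only the demand for detail is unmet. Finally, applying the exemption and section 6.3 forces some judgement of severity, and section 8 says that reasons for departures from the medication regime will be sought.

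Much of this stands. It rules out the claim that these effects are omitted from the trial's data, and it weakens the conflict with section 10. It does not remove the conflict with 10.1 or within 10.2. Nor does it supply the missing detail: an analysis plan can decide to tabulate CRF notes, but it cannot create onset, causality or duration that nobody was required to write down.

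On disease worsening, the safeguards are substantial. HELLP syndrome and proteinuria are secondary endpoints, liver, renal and haematological changes are analysed under 9.2.2, and both oversight committees review clinical outcomes as well as AEs every six months (12.4).

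**Conclusion.** The gastrointestinal exemption is a real fault. It contradicts the protocol's own AE definition and log rule, and for effects known to be common it leaves a poorer primary safety record than the protocol requires for other AEs. A summary based on the AE log would understate those effects. The amount cannot be calculated from the documents; the 2 to 8 women in 20 above rest on assumed rates.

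The disease-worsening exception is a lesser point: a possible misattribution of drug effects that overlap with preeclampsia, limited by the doubt rule, CRF recording and the separate endpoints.

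A reader might infer that the primary safety outcome leaves out the drug's commonest toxicity and much of its serious toxicity. The documents do not support that. The non-severe gastrointestinal effects are on the CRF and fall within the wording of the primary objective. Serious gastrointestinal events, agranulocytosis, aplastic anaemia, severe skin reactions and pneumonitis are not touched by either exception. Other effects that Appendix 1 calls most common, such as headache, pruritus and raised temperature, are not in the gastrointestinal exemption.

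**What to change.** Delete the gastrointestinal exemption in 10.2. Log all nausea, vomiting and diarrhoea as AEs with severity, causality and any resulting dose change, and state that they enter the primary safety summary. Reconcile sections 10, 10.1 and 10.2 so that one rule says what is recorded and where, and correct the reference for *severe* from 10.1 to 10.4.4.

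The cost is small, because the symptoms are already asked about at each contact: revised wording, a longer AE log, and a higher reported AE rate.

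Tabulating laboratory changes by fixed grades, or recording every HELLP-type event before attribution, would reduce the misattribution risk further. The first is analysis-plan detail and the second a debatable design choice, so neither is needed to settle this point.
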